## Abstract

**Background:**

Women living with metastatic breast cancer (MBC) are at risk of significantly impaired quality of life (QOL), symptom burden, distress and fear of progression, and unmet needs, yet they face barriers to accessing evidence-based psychosocial treatments. Our group therefore developed *Finding My Way-Advanced (FMW-A),* a web-based self-guided psychosocial program for women with MBC. This study aims to assess its efficacy in improving mental and other QOL domains, distress, fear of progression, unmet needs, and health service utilisation.

**Methods:**

The multi-site randomised controlled trial (RCT) will enrol 370 Australian participants. Eligible participants are adult (18 years +) women diagnosed with MBC, with a life expectancy of 6 months or more, with sufficient English-language literacy to provide informed consent. Participants will be identified, screened and referred from one of 10 Australian sites, or via self-referral in response to advertisements. Participants complete four online questionnaires: prior to accessing their program (‘baseline’), 6 weeks later (‘post-intervention’), then 3 months and 6 months post-intervention. Consenting participants will be randomised to either *FMW-A* (intervention), or Breast Cancer Network Australia’s (BCNA) online/app resource *My Journey* (minimal intervention attention-control). This is a single-blind study, with randomisation computer-generated and stratified by site. *FMW-A* is a 6-module program addressing some of the most common issues experienced by women with MBC*,* with BCNA control resources integrated within the ‘resources’ section*.* All modules are immediately accessible, with an additional booster module released 10 weeks later. The primary outcome is mental QOL; statistical criteria for superiority is defined as a 4-point difference between groups at post-treatment. Secondary outcomes include other QOL domains, distress, fear of progression, health service use, intervention adherence, and user satisfaction.

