### Statistical methods

#### Sample size and justification

The sample size calculation is based on a repeated measures ANCOVA approach, which takes into account the within-subject correlation across measures, using STATA’s “sampsi” routine and our primary outcome of MQOL. Assuming a between-subject SD of 20 points, 1 baseline measure, and 3 post-baseline measurements per subject (post-treatment, 3-months and 6-months) and a within-subject QOL rho = 0.6, *n* = 147 subjects per group will provide 80% power to detect a clinically meaningful difference in MQOL between treatments of 4 points. Based on attrition rates observed in low-intensity MBC interventions (range 4-20%) and our pilot data to date, we will recruit and enrol 185 subjects per group (total *n* = 370; 46 per recruitment site) to allow for 20% attrition. Based on our pilot data where 71% of eligible women consented, 530 women will be approached (equating to approximately 66 *approached* per recruitment site over the 18-month recruitment window, or 3 to 4 per month), to reach the final sample size of 370.

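### The abstract makes the 4-point target difference the superiority criterion at post-treatment; the sample size and analysis sections use it otherwise or not at all, and nothing reconciles them

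*Protocol article*

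**What the plan says.** Three places in the protocol article bear on how the primary outcome will be judged.

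- **Abstract, Methods:** the "statistical criteria for superiority is defined as a 4-point difference between groups at post-treatment". No other text in the article is labelled a superiority criterion.
- **Sample size and justification:** 147 per group "will provide 80% power to detect a clinically meaningful difference in MQOL between treatments of 4 points". The inputs are given as "Assuming a between-subject SD of 20 points, 1 baseline measure, and 3 post-baseline measurements per subject" and a "within-subject QOL rho = 0.6". Here 4 points is the assumed true effect in a power calculation.
- **Primary analyses:** a linear mixed model with the baseline score as covariate, a group-by-time test, and contrasts that estimate and test group differences at chosen time points. No 4-point threshold appears.

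The Measures section names post-intervention as the primary endpoint, so the abstract's criterion applies at the visit that matters most.

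**The concern.** A target difference and a success threshold do different jobs. The first is the true effect at which the trial should have a good chance of success. The second is what the result must show for success to be declared. Setting both to 4 points at the same visit gives a rule that a treatment with exactly the intended benefit fails half the time, and more patients do not help.

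The abstract and the analysis section can also give different verdicts on the same data: a contrast that is significant against zero but estimated below 4 points is positive under one and not superior under the other. The verdict has consequences. The article makes control participants' first access to the program depend on efficacy being shown, and it describes national scaling if efficacy is evidenced. If both rules stand, the choice between them could be made after the data are seen.

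**Working it through.** **Inputs.** From Sample size and justification: SD 20, within-subject correlation 0.6, one baseline and three post-baseline measures, true difference 4, power 80%, 147 per group before attrition. The article states no alpha. I assume two-sided 0.05, because it reproduces the stated figure; one-sided 0.05 would give 116 per group.

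**Step 1: the plan's own figure.** For repeated measures ANCOVA with r post-baseline measures and one baseline measure, the variance factor is (1 + (r − 1)ρ)/r − ρ².

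- With r = 3 and ρ = 0.6: 2.2/3 − 0.36 = 0.3733.
- Effective SD = 20 × √0.3733 = 12.22.
- n per group = 2 × (1.96 + 0.8416)² × 12.22² / 4² = 146.5, rounded up to 147. Power at 147 is 80.1%.
- Attrition: 147/0.8 = 183.75, so 184 against the stated 185, which is close enough.

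The sample size is therefore sound for the treatment difference averaged over the three post-baseline visits, tested against zero.

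**Step 2: standard errors at 147 per group.** SE = effective SD × √(2/147).

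- Average of three visits: 12.22 × 0.1166 = 1.43. Smallest significant difference: 1.96 × 1.425 = 2.79.
- Post-treatment alone: the variance factor is 1 − 0.36 = 0.64 and the effective SD is 16, so SE = 16 × 0.1166 = 1.87. Smallest significant difference: 1.96 × 1.866 = 3.66.

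**Step 3: the abstract's rule as a threshold on the estimate.** With a true difference of 4, the estimate is centred on 4. So P(estimate ≥ 4) = 1 − Φ((4 − 4)/SE) = 0.50 for any SE, and hence for any sample size, SD or correlation. Also requiring significance changes nothing at 147 per group, because 3.66 is already below 4.

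For an 80% chance of an estimate of at least 4, the true effect would have to be 4 + 0.8416 × SE. That is 5.6 points at post-treatment (SE 1.87), or 5.2 points with the averaged SE of 1.43.

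**Step 4: a test against zero at post-treatment.** Power for a true 4 points is Φ(4/1.866 − 1.96) = Φ(0.18), about 57%.

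| Rule, true effect 4, 147 per group | Chance of success |
|---|---|
| Average of three visits, test against zero (the stated power) | 80% |
| Post-treatment, test against zero | 57% |
| Post-treatment, estimate at least 4 | 50% |

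At post-treatment the two rules disagree for estimates from 3.66 to just under 4. With a true effect of 4 that happens in about 57 − 50 = 7% of trials.

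**The case against.** The best reply is that the abstract never meant a threshold on the estimate. The word observed is not there. The hypotheses speak only of greater improvement, the sample size section treats 4 points as the difference to detect, and the analysis section tests contrasts. All of this fits an ordinary test against zero, with the abstract describing the design difference loosely. This is plausible, and the 50% figure shows a defect only if the sentence is applied as written. But the abstract calls it the statistical criterion for superiority and nothing in the body corrects that, so on this reading the wording is what needs repair.

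Four stronger readings are tempting, and the article does not support them.

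- *Superiority by a 4-point margin.* If the whole confidence interval had to lie above 4, a true 4-point effect would succeed 2.5% of the time. Nothing mentions a margin or a confidence limit set against 4, and the power calculation points the other way.
- *Non-significant results will be called superior.* At 147 per group an estimate of 4.0 has z = 4/1.866 = 2.14, p about 0.03. The reverse needs about 122 per group (the pilot's 66% retention applied to 185, against the 20% attrition planned), and even then p is 0.051.
- *Rewording recovers the 80%.* It does not. At post-treatment the gap is 50% against 57%, and at 122 per group (SE 2.05) the test against zero also succeeds about 50% of the time. A test gains power with more patients and a point threshold does not, but most of the shortfall from 80% comes from using one visit instead of the three-visit average.
- *The missing alpha is itself a fault.* A condensed article may leave that to the full protocol or SAP.

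**Conclusion.** The inconsistency is real and should be settled before analysis. The abstract states a decision rule at the primary endpoint that the sample size section does not power and the analysis section does not use. Taken literally, that rule gives a 50% chance of success at the intended effect, a result that depends on no input beyond an unbiased, symmetrically distributed estimate.

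The practical disagreement with a test at post-treatment is narrow: estimates from about 3.7 up to 4 points at 147 per group. That band rests on SD 20, correlation 0.6, complete data at that visit and two-sided alpha 0.05, the last of which is my assumption.

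The finding does not show that the sponsor intends a point threshold, and it does not touch the figure of 147, which reproduces.

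**What to change.** Before analysis, state in the protocol and the SAP that superiority means a baseline-adjusted between-group difference in emotional functioning at post-treatment, favouring FMW-A, whose two-sided 95% confidence interval excludes 0. Keep 4 points in two roles only: the difference used in the sample size calculation, and the clinical-relevance benchmark against which the estimate and its interval are reported.

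In the same revision, attribute the 80% power to the average of the three post-baseline visits, and give the post-treatment contrast its own figure, about 57% at 147 per group on the plan's inputs.

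The cost is a rewording; recruitment, data collection and the model are unchanged. The downside is that a significant result below 4 points would have to be reported as superior but of uncertain clinical relevance. The rewording also leaves the lower power at post-treatment as it is.

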**Discussion:**

This will be the first adequately powered RCT of a self-directed online intervention for women with MBC. If efficacious, *FMW-A* will help address two national key priorities for management of MBC – enhancing QOL and reducing symptom burden. *FMW-A* has the potential to address unmet needs and overcome access barriers for this overlooked population, while reducing health system burden.

**Trial registration:**

The study was registered prospectively with the ANZCTR on 29/10/2021. Trial ID ACTRN12621001482853p. https://anzctr.org.au/Trial/Registration/TrialReview.aspx?id=382714&isReview=true

**Supplementary Information:**

The online version contains supplementary material available at 10.1186/s12885-022-10410-z.

## Background

In 2020 alone, 2.3 million women globally were diagnosed with breast cancer, and 7.8 million women alive were diagnosed with breast cancer in the past 5 years, making it the world’s most prevalent cancer [1]. Of those diagnosed, approximately 5% would have received the diagnosis of metastatic breast cancer (MBC) as their first diagnosis (‘de novo’), and a further 10% experienced a recurrence/progression of prior primary breast cancer [2]. Despite improved treatments and survival duration, with some women experiencing extended survival of 10 years or longer [3], MBC remains the leading cause of female cancer mortality, with an estimated 685,000 deaths globally in 2020 [1].

Women receiving a diagnosis of MBC experience significant challenges; in addition to managing their awareness of premature mortality, they also face a more proximal future of progressing illness; physical symptoms, including pain, fatigue, and insomnia; and resulting functional limitations, such as reduced mobility or ability to undertake usual occupation/roles [4, 5]. Clinically elevated distress, psychiatric disorders, and impaired quality of life (QOL) typically occur in 35-43% of women following diagnosis of MBC [4, 5], compared to 20% in the general community. Left untreated, distress and impaired QOL can result in increased health burden [6] via reduced ability to tolerate physical symptoms and treatment toxicities, which then require further treatment [7]; reduced adherence to cancer treatments or lifestyle recommendations [8]; and increased requests for additional investigations outside scheduled visits [9]. As a result, lead national cancer control agencies argue for managing symptoms and optimising QOL as key treatment targets for MBC [2].

Yet the high levels of unmet needs, distress, symptom burden, and impaired QOL that women with MBC experience remain largely unaddressed, with research finding these women are underserviced and receive less support than women with early-stage disease [10]. Indeed, a 2015 Breast Cancer Network Australia (BCNA) survey of 582 individuals with MBC found that 68% of respondents had unmet needs, with the top three being fear of progression, fatigue, and uncertainty about the future [11]. ‘Self-care’ (including web-based interventions) was the preferred management strategy for the latter two needs, and the second-preferred option (after oncologist-involvement) for managing fear of cancer progression.

While psychological interventions have an arguably prominent role in managing all three of these unmet needs, few resources have been developed for this population, particularly resources that utilise self-care and support self-management. Indeed, our 2018 systematic review of interventions for MBC identified only 15 RCTs that have been conducted to date [12]: Overall, interventions improved distress, coping, and pain. For quality of life, sleep, and fatigue, the evidence was insufficient to form recommendations [12]. Since 2018, four additional RCTs have been published (two group-based, one individual-based, one low intensity) [13–16]. Three were pilot trials which found evidence of feasibility [13–15], while the fully powered RCT of a 12-month weekly group program found evidence of improved depression, anxiety, and QOL compared to a no-treatment control [16]. Overall, group therapy has the strongest evidence base with nine published trials [12, 16], but had the correspondingly poorest uptake/adherence [12]. The intensity of these services/interventions precludes participation by women with high symptom burden, who live in rural/remote areas, are living with socioeconomic disadvantage, or have occupational or carer demands. Personal barriers to seeking psychological interventions also exist, including perceived stigma [17], and fear of being distressed by others’ decline or death [18]. There are also significant workforce barriers, where the demand for existing psychological services exceeds supply [19]. In contrast, while low-intensity interventions (to date) have the weakest evidence base (five trials published: three telephone-based, two expressive writing, nil online), they have the highest uptake and adherence [12, 14]. In sum, given women with MBC face intensive medical treatment schedules, are frequently unable to commit to future appointments, and may have compromised health status [11, 12], future research needs to design and trial interventions that can yield efficacy while minimising participation burden.

Digital health tools, such as web-based therapy, could address these barriers. Given digital health tools provide 24/7 access at a time and place convenient to the patient, and reduce obligations to spend valued time and money in healthcare settings, this mode of providing psychosocial care has particular pertinence to women with MBC [20]. Furthermore, digital interventions are easily scalable, can be immediately updated as new evidence emerges, and provide the flexibility to explore content in a non-linear way, with patients able to access information pertinent to their most immediate needs [21]. While there are no published online intervention RCTs in this population, women with MBC are already seeking cancer-related information on the internet [20] and are receptive to the online provision of a psychosocial program [22]. The rapidly building evidence base in *early-stage* cancer populations for improving distress [23, 24], depression and anxiety [25], fear of recurrence [26], QOL [27, 28], and health service utilisation [27], can help to inform future MBC-specific intervention development.

Our team recently developed and usability-tested an online program to support women with MBC: *Finding My Way-Advanced (FMW-A)* [29]. FMW-A was co-designed, with content initially sourced and adapted from our evidence-based *Finding My Way* web-program for people with *early-stage* cancer [27, 28]. The content was authored by a senior clinical psychologist with expertise in psycho-oncology (LB), with iterative rounds of input and feedback from a multidisciplinary co-design team including consumers, clinicians, and academics. A qualitative think-aloud protocol was then implemented to test usability of the resulting 6-module prototype, with women living with MBC accessing up to three modules with an interviewer sitting alongside. Feedback summarised the supportive and informative nature of the program, supplemented by comments about broadly relatable content. However, within themes, diverging experiences emerged regarding navigability, worksheets and layout. Participants noted that having/making time for the intervention would be important to program engagement [29]. Pragmatic issues were corrected prior to feasibility pilot testing, which demonstrated feasibility via an uptake rate of 61%, a retention rate of 66%, and an engagement level of 2.3 modules [30], which was in line with prior online intervention research, and sufficient to impact outcomes [27].

Digital health tools have the potential to facilitate scalable access to cost-effective interventions and address inequity, however none have been trialled in a large-scale RCT in MBC. While digital health solutions have proliferated in the general community, they lack the required essential evidence of efficacy, safety, acceptability, accessibility, and content-relevance for this vulnerable population [31].

This study aims to address the unmet needs of women diagnosed with MBC to improve their QOL and wellbeing, and ultimately reduce the health system burden [4–6].

## Specific objectives

### Primary objective

The primary objective of the *Finding My Way-Advanced* randomised controlled trial (RCT) is to evaluate the efficacy of the intervention (‘FMW-A’) compared with an online minimal-intervention attention control (‘control’) in improving mental QOL, as measured by the ‘emotional functioning’ subscale of the European Organisation for Research and Treatment of Cancer Quality of Life Core Questionnaire (EORTC QLQ C-30), in women with MBC. The term ‘mental QOL’ was selected for this study to enable easier comparison to the broader QOL literature where mental QOL is the predominant term.

### Secondary objectives

Secondary objectives are to:i.Evaluate the efficacy of FMW-A compared to control in improving other health-related QOL domains, psychological distress, fear of progression, unmet needs, and health service utilisation in women with MBC.ii.Describe uptake to the RCT and adherence to the program.iii.Evaluate the cost-effectiveness of the program.

### Hypotheses

Primary hypothesis:Intervention participants will report greater improvements in the primary outcome of mental QOL (MQOL) compared to minimal-intervention control participants from baseline to post-intervention, with effects sustained at 3- and 6-month follow-ups.

Secondary hypotheses:Intervention participants will report greater improvements from baseline to post-treatment in secondary well-being outcomes, i.e., physical, social, cognitive, role and global QOL domains; fear of progression; psychological distress; and unmet needs, compared to control participants, with effects sustained at 3- and 6-month follow-ups.Intervention participants will have lower health service utilisation and public hospital admissions (indicator of cost savings to the health service) over the 6-month follow-up period, compared to control participants.

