### Measures

Table 2 outlines the efficacy outcomes that will be assessed using a battery of validated self-report measures at baseline, post-intervention (primary endpoint), 3-month and 6-month follow-ups, supplemented with website usage data and patient health service use data obtained via data linkage of government databases (‘Services Australia’). Figure 3 outlines the schedule of assessments.

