### Primary analyses

Linear Mixed Models (LMM) will be employed following completion of data collection to examine the efficacy of the intervention, in line with the statistical methodology utilised in previous trials our group has published [27, 28]. Analysis will be by intention to treat, defined as all patients who register. LMM will be used to model all continuous outcomes while accounting for covariance between repeated measures on patients and adjusting for baseline measures, which improves precision of estimation of effects. These models will allow for comparing patterns of change over time by testing group by time interaction, and estimating and testing differences between groups at time points of interest via linear contrasts. Mixed models are valid for data that are missing completely at random and missing at random; patterns of missing data will be considered to assess potential missing data mechanisms. In the present study, the fixed main effects will be treatment condition (intervention, control), and time (post-treatment, 3-month, 6 month), with the baseline measure of the outcome entered as a covariate. A random subject effect will be entered into the model to allow the trajectory of each individual to differ by a constant elevation from the group trajectory. Between-group effect sizes and reliable change indices will be calculated to provide a measure of the magnitude and clinical significance of changes, respectively. No interim analysis is planned.

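### The primary hypothesis includes effects 'sustained' at 3 and 6 months, but superiority is decided at post-intervention alone, and the protocol does not say whether durability is part of the primary claim

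*Protocol article*

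**What the plan says.** Four parts of the protocol article bear on what counts as success for mental QOL.

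- **Hypotheses.** The sentence labelled as the primary hypothesis predicts greater improvement than control "from baseline to post-intervention, with effects sustained at 3- and 6-month follow-ups". The durability clause sits inside that sentence and is not marked as secondary. The secondary objectives do not take it up for mental QOL, since they concern the other QOL domains and other outcomes.
- **Abstract, Methods.** The "statistical criteria for superiority is defined as a 4-point difference between groups at post-treatment".
- **Measures.** The assessment times are baseline, "post-intervention (primary endpoint), 3-month and 6-month follow-ups". Only the first post-baseline visit carries the primary label.
- **Primary analyses.** The mixed model serves for "comparing patterns of change over time by testing group by time interaction", and for "estimating and testing differences between groups at time points of interest via linear contrasts". The time points of interest are not named.

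Sample size and justification adds a further element. It is based on repeated-measures ANCOVA: "Assuming a between-subject SD of 20 points, 1 baseline measure, and 3 post-baseline measurements per subject", a "within-subject QOL rho = 0.6", and a "clinically meaningful difference in MQOL between treatments of 4 points". This gives 147 per group for 80% power, raised to 185 per group for 20% attrition.

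**The concern.** The hypothesis has two limbs (benefit at T1, and persistence at T2 and T3), while the superiority criterion and the endpoint label have one (T1). If T1 is positive and T2 or T3 is not, one part of the document declares superiority and another leaves the primary hypothesis unsupported. No passage says which governs, or that durability is only supportive.

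'Sustained' also has no operational meaning. It could require a significant difference at each visit, or only no significant decline after T1. These are very different hurdles, and the choice between them could be made once the results are known.

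A fading effect is a practical possibility here. The weekly email reminders stop after six weeks, and a single booster module follows at ten weeks.

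**Working it through.** **Inputs** (Sample size and justification): SD 20, rho 0.6, one baseline and three post-baseline measures, difference 4, 147 per group.

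**Assumptions not in the document:** two-sided 5% tests, compound symmetry at all visits, no missing data.

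**1. Reproduce the plan's figure.** For the baseline-adjusted mean of r post-baseline visits, the variance factor is (1 + (r − 1)ρ)/r − ρ².
- r = 3: (1 + 1.2)/3 − 0.36 = 0.3733.
- n per group = 2 × (1.96 + 0.8416)² × 400 × 0.3733 / 4² = 146.5, so 147 (power 80.1%).
- 147/0.8 = 183.75, so 184, against 185 stated.

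The stated size reproduces, which supports the two-sided 5% assumption (one-sided 5% gives 116). It is the size for the average of T1, T2 and T3.

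**2. Power at T1 alone.** With r = 1 the factor is 1 − 0.36 = 0.64.
- SE = √(2 × 400 × 0.64/147) = 1.866.
- 4/1.866 = 2.143; power = Φ(2.143 − 1.96) = 57.3%.
- With all 185 per arm analysed: SE 1.664, power 67.2%.
- For 80% power at T1: 2 × (1.96 + 0.8416)² × 400 × 0.64/16 = 251.2, so 252 per group.

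**3. Joint behaviour of the three contrasts.** After baseline adjustment, the correlation between any two visit contrasts is (0.6 − 0.36)/(1 − 0.36) = 0.375. The SE of the difference between two visit contrasts is 1.866 × √(2 × (1 − 0.375)) = 2.087. Probabilities come from the trivariate normal with this structure.

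| 147 per arm | True effect 4, 4, 4 | True effect 4, 2, 2 |
|---|---|---|
| T1 significant | 57.3% | 57.3% |
| Significant at T1, T2 and T3 | 28.6% | 5.8% |
| T1 significant, not significant at every visit | 28.6% | 51.5% |
| T1 significant, with a significant decline from T1 to T2 or T3 | about 4% | about 22% |

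The third row is the rate at which the two parts of the plan disagree if 'sustained' means significant at each visit (57.3 − 28.6, and 57.3 − 5.8, to rounding). The fourth row is the rate if it means no significant decline.

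**4. Null case.** With no true effect at any visit, at least one of the three contrasts has |z| > 1.96 in about 13% of trials. At T1 alone the rate is 5%.

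**The case against.** The strongest reply is that a hypothesis states an expectation and is not a decision rule. The deciding time point is given twice, consistently, as post-intervention. The durability clause trails the main claim, and the same words are attached to the secondary hypotheses, so it may be a standard description of the expected trajectory. This has weight: no passage says that superiority requires T2 and T3. But the sentence is labelled primary, a results paper will report whether it was supported, and nothing calls durability supportive.

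Three stronger readings are tempting but not supported.

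- **The passages conflict in 29% of trials.** That figure needs 'sustained' to mean significance at every visit. Under the weaker reading it is about 4%, and the document does not choose.
- **The type I error is 13%.** That would need a rule allowing success at any positive visit. No passage states one, and with T1 fixed the rate is 5%.
- **The 57% is the chance of meeting the superiority criterion.** It is the power of a significance test, equivalent to an observed T1 difference above about 1.96 × 1.866 = 3.7 points. The Abstract's criterion, taken literally as an observed difference of at least 4, would be met in 50% of trials when the true difference is 4.

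An article may also leave testing order to an analysis plan, so the absence of a hierarchy is not itself the defect. The defect is that the published statements of the primary claim do not agree.

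**Conclusion.** The inconsistency is real and should be corrected; it is mainly one of wording. The protocol does not settle whether durability at 3 and 6 months belongs to the primary claim, and it gives 'sustained' no test. With a constant 4-point effect, T1 is significant while the durability clause fails in about 4% to 29% of trials; with an effect of 4, 2, 2 it is about 22% to 52%. The ends of each range are the two readings of 'sustained'. All four figures rest on 147 per arm and the assumptions listed in the working.

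The power shortfall at T1 is part of the same problem: the trial is sized for a quantity, the three-visit average, that neither the hypothesis nor the superiority criterion names.

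**What to change.** 1. In Hypotheses, make the T1 between-group contrast the only primary hypothesis for mental QOL, matching the Abstract and Measures, and name that contrast in Primary analyses.
2. Move durability to a secondary hypothesis with a stated test. One option is a fixed sequence after T1: T2, then T3, each at two-sided 5%, stopping at the first non-significant result. 'Sustained' at a visit then means that the contrast at that visit is itself positive and significant.
3. Restate Sample size and justification at the same time. It should say that 147 per group gives 80% power for the average of the three post-baseline visits and about 57% for the T1 contrast (about 67% if all 185 per arm are analysed), with the alpha level and sidedness stated.

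The first two changes cost a few sentences and need no new data. Under the fixed sequence, T3 cannot be claimed if T1 or T2 fails. The third discloses that a T1-only primary test is underpowered at the planned size: 80% would need 252 per group under the same inputs. Rewording the hypothesis does not remove that shortfall.
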